### Secondary Endpoints for Efficacy

Descriptive analyses of the secondary endpoints will be performed in similar regression models as for the primary endpoint, as appropriate for the respective type of data. Differences between treatment groups will be calculated with 95% CIs. Progression free survival and complete remission will be measured from randomisation and be analysed using Cox regression as described for the primary endpoint. Endpoints with competing events will be estimated using the Aalen Johanson estimator. Endpoints without competing events with be estimated using the Kaplan Meier estimator. Quality of life measures (EORTC QLQ-C30, QLQ-CR29 and QLQ-LC29) will be analysed descriptively by treatment arm and time point using linear regression. Changes from baseline will be described. Differences in the number of courses of systemic therapy and in the time on systemic therapy will be summarised descriptively by treatment arm using the FAS. The impact of the mutational status on treatment response and survival (on PFS and OS) performed in similar regression models as for primary endpoint adjusted for the mutational status.

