### Endpoints

The primary endpoint is overall survival (OS). OS is defined as the time from randomisation until death from any cause with censoring at the last date alive. The primary objective is to assess the effect of pulmonary metastasectomy compared to standard of care consisting of systemic therapy and possible SBRT where indicated on OS.

Secondary endpoints are

Progression-free survival (PFS), defined as the time from randomisation until disease progression or death from any cause.PFS assessment will be performed locally, usually in a multidisciplinary setting (e.g. tumour board) but at least by a radiologist and oncologist/thoracic surgeon.Definitions of progressive disease (PD) can consist of but are not limited to: unequivocal tumour growth of known metastatic lesions, new metastatic lesions, local recurrence.PFS will be determined from serial CT scans, PET-CT or MRT with censoring at the last date alive and progression-free.Complete remission, defined as no radiologic sign of residual disease and pathologically complete (R0) resection if applicable.Quality of life (QoL) using the EORTC QLQ-C30, QLQ-CR29 and QLQ-LC29 questionnaires at 3, 6, 12, 24 and 36 months after randomisation.

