### Primary Endpoint

The effects of standard of care with and without metastasectomy with respect to the primary endpoint overall survival will be estimated and tested by Cox regression. The regression model will include treatment and trial site as independent variables, as well as, metachronicity vs. synchronicity and, previous treatment of hepatic metastasis and colon- or rectal cancer. As estimate of the effect size, the hazard ratio between the two treatment arms will be given with the corresponding asymptotic two-sided 95% confidence interval. The two-sided test on difference between standard of care with metastasectomy and standard of care at significance level 5% will be based on the corresponding asymptotic two-sided 95% confidence interval from the Cox regression model. Overall survival will be analysed irrespective of the occurrence of intercurrent events. This is consistent with the treatment policy strategy of the estimands framework.

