Nevertheless, multiple prospective randomised trials suggest a survival benefit from radical local treatments in oligometastatic cancers (9–11). Hence there is an urgent need for more homogeneous and adequately powered trials in CRC. Considering the discussed issues regarding the heterogeneity in the patient collective, complexity of treatment trajectories, regional differences in treatment choices as well as the aforementioned various biases, well-powered clinical trials have been challenging to design and execute. The goal of this study is to create a setting which allows treatment as close to the real-life conditions as possible but under well standardised conditions. Based on previous trials, in which patient recruitment in the given setting hindered successful study completion, we decided to (1) restrict inclusion to patients with 3 or more metastases (since in case of lesser, surgery will probably be the preferred option) and (2) allow for real world standard of care treatment options before and after randomization including watchful waiting (as opposed to a predefined treatment protocol) and (3) possibility that patient can receive SOC externally (to reduce patient burden). Moreover, we chose to stipulate 12 weeks of systemic treatment prior to possible resection to further standardize treatment response and disease course over a certain period of time. Hence, included patients will be in the disease state of oligopersistence. To increase the feasibility of the trial we took several measures to minimize documentation burden: e.g. certain events are only documented in the experimental arm and radiology data on disease progression is limited to no evidence of disease and evidence of disease, which is then further differentiated into progressive and non-progressive disease. Furthermore, to adequately assess the treatment burden, we included quality of life questionnaires, evaluations regarding the application of chemotherapy, as well as nights spend in hospital. This should reflect the possible negative impact of surgery but also chemotherapy on quality of life during the course of the disease. Finally, novel biomarkers are needed for better risk stratification and identification of patients with high risk for CRC recurrence after surgical metastasectomy, outperforming conventional parameters such as CEA, number of metastases, or the disease-free interval. Therefore, in selected centres circulating DNA (ctDNA) will be analysed at various pre- and post-surgical time points as well as in patients not undergoing surgery to characterize its role as a clinically useful biomarker in patients with mCRC undergoing curative-intent pulmonary metastasectomy within the prospective PUCC trial. With further, well-standardised prospective data we hope to provide stronger evidence for performance of PM and potentially better patient selection.

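### The QoL regression as described does not name the baseline score as a covariate, which costs precision, and its late-visit comparisons are open to selection by death and non-response

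*Protocol article*

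**What the plan says.** All references are to the protocol article.

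- **Endpoints** makes QoL (three EORTC questionnaires) a secondary endpoint, assessed "at 3, 6, 12, 24 and 36 months after randomisation".
- **Secondary Endpoints for Efficacy** sets the general rule: "Descriptive analyses of the secondary endpoints will be performed in similar regression models as for the primary endpoint", adapted to the type of data. It adds: "Differences between treatment groups will be calculated with 95% CIs".
- For QoL the same section says that the scales "will be analysed descriptively by treatment arm and time point using linear regression", followed by: "Changes from baseline will be described".
- **Primary Endpoint** gives the model referred to: "The regression model will include treatment and trial site as independent variables", together with "metachronicity vs. synchronicity and, previous treatment of hepatic metastasis and colon- or rectal cancer". No QoL score is in this list.
- **Discussion** states the purpose: "to adequately assess the treatment burden, we included quality of life questionnaires". It names these together with data on chemotherapy and nights in hospital.

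The text on QoL mentions no repeated-measures model and does not say how death or missing questionnaires are treated.

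**The concern.** A baseline score is evidently planned, since changes from it are to be described, but nothing places it in the regression. A patient's own starting score is usually the strongest predictor of later scores. Leaving it out widens every interval, including those at month 3, when any burden of surgery is most likely to show.

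The second issue is who contributes at each visit. On its natural reading, the sentence describes a regression on whoever answers at that visit, without use of their other scores. If the trial's survival hypothesis is true, the control arm will have lost many more patients by months 24 and 36. If patients with poor QoL leave sooner, the remaining controls are the more strongly selected group, and the late comparison is tilted against surgery.

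The differences and intervals will be read as evidence on treatment burden, whatever label the analysis carries.

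**Working it through.** **Inputs from the article (Biostatistical Planning and Analysis).** Median overall survival 27 months (control) and 55 months (surgery), hazard ratio 2.04, two-sided 5%, 90% power, 83 events, 76 patients per arm, 2 years' recruitment plus 3 years' follow-up.

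**Inputs not in the documents, therefore assumed.** Baseline-to-visit correlation r = 0.3 to 0.7, QoL standard deviation 20 points, and the strength of the link between QoL and leaving the study.

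**1. The plan's own figure.** No figure is given for QoL. The survival inputs can be checked: 55/27 = 2.04, and Schoenfeld's formula gives 4 × (1.960 + 1.282)² / (ln 2.04)² = 83 events, as stated. With exponential survival and uniform accrual, the probabilities of death are 0.704 and 0.452, so 76 × (0.704 + 0.452) ≈ 88 events are expected. The plan's survival figures are coherent and can be carried over to QoL attrition.

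**2. Precision.** Baseline adjustment multiplies the standard error by √(1 − r²). This takes the other covariates to explain little of the score. Analysing change scores without adjustment gives a standard error √(2/(1 + r)) times the adjusted one. The half-width is 1.96 × 20 × √(2/76) = 6.4 points unadjusted, with all 76 per arm answering.

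| r | Variance cut | Unadjusted SE / adjusted SE | Change-score SE / adjusted SE | 95% half-width, adjusted |
|---|---|---|---|---|
| 0.3 | 9% | 1.05 | 1.24 | 6.1 |
| 0.5 | 25% | 1.15 | 1.15 | 5.5 |
| 0.7 | 49% | 1.40 | 1.08 | 4.5 |

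At r = 0.5 the gain equals 1/0.75 = 1.33, a third more patients.

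**3. Patients alive.** 76 × 0.5^(t/median):

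| Month | Control | Surgery |
|---|---|---|
| 3 | 70 (93%) | 73 (96%) |
| 6 | 65 (86%) | 70 (93%) |
| 12 | 56 (74%) | 65 (86%) |
| 24 | 41 (54%) | 56 (74%) |
| 36 | 30 (40%) | 48 (63%) |

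These losses are deaths. Non-response comes on top.

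**4. Possible selection.** A simulation with no true QoL effect let the hazard of leaving be (ln 2/median) × exp(−g × previous score in SD units). Entries are the spurious surgery-minus-control difference in points, shown as the range over r = 0.3, 0.5 and 0.7.

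| g | Month 3, no baseline | Month 24, no baseline | Month 36, no baseline | Month 36, baseline added |
|---|---|---|---|---|
| 0 | within 0.1 of zero | within 0.1 of zero | within 0.1 of zero | within 0.1 of zero |
| 0.3 | −0.1 to −0.2 | −0.5 to −1.3 | −0.8 to −2.1 | −0.5 to −0.7 |
| 0.5 | −0.2 to −0.3 | −0.9 to −2.0 | −1.3 to −2.9 | −0.9 to −1.0 |

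For scale, the month-36 standard error with SD 20 is 20 × √(1/30.2 + 1/48.3) = 4.6 points.

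A second simulation (SD 22, correlation 0.48 to 0.59, extra non-return of 0.5% per month, all assumed) gave −1.6 points at month 24 and −2.0 at month 36 without baseline, and 0.1 or less in size with a baseline-adjusted repeated-measures likelihood analysis. That last result follows from its design: leaving depended only on the previous observed score, which is the missing-at-random condition, and deaths were treated like missing questionnaires.

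**The case against.** Three stronger readings are tempting, and the documents do not support them.

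- **That the plan excludes the baseline score.** No sentence does. Its absence is inferred from a covariate list written for a survival model, and the article lets secondary models vary with the data type. The full protocol or analysis plan may add the score. What stands is that the article names a method and a covariate source, and neither contains it.
- **That separate regressions per visit are fixed.** This is the natural reading, but a single regression with arm and time as terms also fits the words. That reading would not restore the baseline score. If it treated a patient's five scores as independent, at a within-patient correlation of 0.5 it would understate the variance of a visit-averaged difference threefold (1 + 4 × 0.5).
- **That the QoL comparison is biased.** The documents give no link between QoL and leaving the study. Without such a link the bias is about zero.

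The strongest objection concerns the target. If the aim is to describe patients alive at each visit, the difference among survivors is the direct summary and is not biased for that aim. A mixed model implicitly estimates scores as though nobody had died, so it does not cure late-visit selection by death. This stands, and it limits what the repeated-measures model can be said to repair to questionnaires missing among living patients.

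It is also true that the analysis is labelled descriptive, that QoL is one of several burden measures, and that the simulated bias is smaller than its standard error. None of this removes the precision loss, which needs no assumption about dropout.

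**Conclusion.** The point holds in a limited form. As written, the QoL comparison forgoes a nearly free gain in precision: the standard error is about 5% to 40% larger than needed for correlations of 0.3 to 0.7, an assumed range.

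The comparisons at months 24 and 36 are open to selection bias, because the plan's own medians imply very unequal survival. The direction would be against surgery. The size, roughly 1 to 3 points at month 36, depends wholly on an assumed link between QoL and leaving the study. At month 3 it is at most about 0.3 points. Baseline adjustment alone reduces the month-36 figure to between 0.5 and 1.0 points in those scenarios but does not remove it.

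The primary endpoint and sample size are not touched. The change is worth making before analysis, as an improvement to a secondary endpoint.

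**What to change.** Replace the QoL sentence with wording such as:

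*Each QoL scale is analysed in one mixed model for repeated measures with arm, visit, arm-by-visit, baseline score, baseline-by-visit and the covariates of the primary model. Arm differences with 95% confidence intervals are given at each visit. Questionnaires missing among living patients are handled under missing-at-random. The numbers alive and the numbers answering are reported by arm and visit. Differences at months 24 and 36 are to be read as QoL while alive, since the model does not resolve truncation by death.*

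If the simpler regression is kept, the minimum change is to add each scale's baseline score as a covariate. In either case, show the observed means of living, answering patients beside the model estimates, because a label alone does not change what a mixed model estimates.

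The cost is a change of wording and slightly more analysis work. No new data are needed, since describing changes already requires a baseline score.

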## Abstract

This is a multicentre prospective randomised controlled trial for patients with 3 or more resectable pulmonary metastases from colorectal carcinoma. The study investigates the effects of pulmonary metastasectomy in addition to standard medical treatment in comparison to standard medical treatment plus possible local ablative measures such as SBRT. This trial is intended to demonstrate an overall survival difference in the group undergoing pulmonary metastasectomy. Further secondary and exploratory endpoints include quality of life (EORTC QLQ-C30, QLQ-CR29 and QLQ-LC29 questionnaires), progression-free survival and impact of mutational status. Due to the heterogeneity and complexity of the disease and treatment trajectories in metastasised colorectal cancer, well powered trials have been very challenging to design and execute. The goal of this study is to create a setting which allows treatment as close to the real life conditions as possible but under well standardised conditions. Based on previous trials, in which patient recruitment in the given setting hindered successful study completion, we decided to (1) restrict inclusion to patients with 3 or more metastases (since in case of lesser, surgery will probably be the preferred option) and (2) allow for real world standard of care (SOC) treatment options before and after randomisation including watchful waiting (as opposed to a predefined treatment protocol) and (3) possibility that patient can receive SOC externally (to reduce patient burden). Moreover, we chose to stipulate 12 weeks of systemic treatment prior to possible resection to further standardize treatment response and disease course over a certain period of time. Hence, included patients will be in the disease state of oligopersistence rather than primary oligometastatic. The trial was registered in the German Clinical Trials Register (DRKS-No.: DRKS00024727).

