### Biostatistical Planning and Analysis

The sample size calculation is based on the primary endpoint overall survival. A median OS time of approximately 27 months under standard of care is assumed, while the median OS time is expected to increase to about 55 months under standard of care (without SBRT) and pulmonary metastasectomy (2, 21). This corresponds to a hazard ratio of 2.04 between the treatment arms (medical treatment vs. medical treatment and pulmonary metastasectomy). The effect of medical treatment and pulmonary metastasectomy will be assessed by a log-rank test at two-sided significance level of 5% and by estimation of the hazard ratio with corresponding asymptotic two-sided 95% confidence interval. The null hypothesis is rejected, if the confidence interval does not contain one. Under the above assumptions, the trial is planned to detect a difference between medical treatment and pulmonary metastasectomy over medical treatment alone with a power of 90%, which requires a total number of 83 events to be observed. To account for the possibility that the observed hazard ratio may be diminished by non-compliance and/or drop-out of patients, the sample size is calculated to achieve a power of 90%. The required number of patients to be randomised to observe this amount of events depends on the length of follow-up. With a recruitment period of 2 years, an additional follow-up period after the end of recruitment of 3 years (maximum length of follow up 5 years) it can safely be assumed that a sufficient number of events will have been observed by the end of the trial if a total of 152 patients (76 per group) are available for analysis (software used, e.g. nQuery Advisor 8.3).

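### The stated mutational-status model shows whether mutation is prognostic, but not whether the effect of metastasectomy differs by mutational status

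*Protocol article*

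**What the plan says.** The last sentence of Secondary Endpoints for Efficacy sets both question and method. The question is "The impact of the mutational status on treatment response and survival (on PFS and OS"); the analysis is to be "performed in similar regression models as for primary endpoint adjusted for the mutational status".

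The model referred to is in the section Primary Endpoint: "The regression model will include treatment and trial site as independent variables, as well as, metachronicity vs. synchronicity and, previous treatment of hepatic metastasis", followed by colon versus rectal cancer. All of these are main effects. The article states no interaction term, subgroup analysis or mutation-specific treatment effect.

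The Abstract places the topic in a list that opens "Further secondary and exploratory endpoints include quality of life" and goes on to "progression-free survival and impact of mutational status". The Endpoints section does not list it among the secondary endpoints, and the secondary analyses are described as descriptive.

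**The concern.** In a randomised comparison, mutation can matter in two ways. It may be prognostic: mutated patients do better or worse whatever their arm. It may also be predictive: surgery helps one mutation group more than the other. Randomisation allows the second question to be answered without confounding of the treatment contrast, but only if the model lets the treatment effect vary by mutation.

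A model that only adjusts for mutation assumes the same surgery HR in mutated and wild-type patients. If the true effects differ, the report would still show one treatment HR and one mutation HR under the label of an impact of mutational status. A reader could then take a prognostic HR for evidence on who responds to surgery. Part of a real difference in effect could also surface as an apparently stronger prognostic effect.

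**Working it through.** **The plan's own figure.** Inputs from Biostatistical Planning and Analysis: HR 2.04 (control versus surgery), two-sided 5%, power 90%; 1:1 allocation. Schoenfeld's formula gives 4 × (1.960 + 1.282)² / (ln 2.04)² = 42.03 / 0.508 = 82.7, so 83 deaths. The stated 83 reproduces and is not in dispute.

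**What each model can estimate.** Let T = 1 for surgery and M = 1 for mutated.

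- Adjusted model: log hazard = baseline + b1·T + b2·M + other covariates. The surgery HR is exp(b1) in both mutation groups, so their ratio is 1 by construction. exp(b2) is the prognostic HR.
- Model with interaction: add b3·T·M. The surgery HR is exp(b1) in wild-type and exp(b1 + b3) in mutated patients; the ratio of HRs is exp(b3).

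**Illustration by large simulation.** Assumptions not in the documents: 40% of patients mutated, prognostic HR 1.3. Taken from the plan: control median 27 months (used here for wild-type controls), 24 months of accrual and 36 months of further follow-up. There were 20,000 simulated patients per scenario.

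| True surgery HR, wild-type / mutated | Adjusted model: surgery HR | Adjusted model: mutation HR | Interaction model: ratio of HRs |
|---|---|---|---|
| 0.49 / 0.49 | 0.48 | 1.30 | 1.03 |
| 0.35 / 0.74 (true ratio 0.74/0.35 = 2.11) | 0.51 | 1.77 | 2.18 |

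The adjusted model returns almost the same surgery HR in both scenarios. In the second, the difference in effect shows up as a mutation HR of 1.77 instead of 1.3. Only the interaction model separates the two.

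**Precision of an added interaction at 83 deaths.** Let p be the share of deaths in mutated patients. The documents do not give it; 0.2 to 0.6 is assumed. Mutation status is taken as known for every death.

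SE of the log ratio of HRs = √[4/(83p) + 4/(83(1 − p))]. At p = 0.5 this is √(0.0964 + 0.0964) = 0.439. The CI factor is exp(1.96 × SE), and the ratio detectable with 80% power is exp(2.80 × SE).

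| p | SE | 95% CI factor | Power for a ratio of 2.04 | Ratio with 80% power |
|---|---|---|---|---|
| 0.2 | 0.549 | 2.93 | 25% | 4.65 |
| 0.3 | 0.479 | 2.56 | 32% | 3.83 |
| 0.4 or 0.6 | 0.448 | 2.41 | 36% | 3.51 |
| 0.5 | 0.439 | 2.36 | 37% | 3.42 |

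For comparison, the SE of the overall log HR at 83 deaths is 2/√83 = 0.22. An interaction as large as the planned main effect (ratio 2.04) would need about 248 deaths at p = 0.5 and 387 at p = 0.2 for 80% power.

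**The case against.** The strongest reply is that the sentence makes mutational status the exposure and makes response, PFS and OS the outcomes. It does not mention treatment arms or prediction, and a covariate-adjusted model answers it. The Discussion also uses the phrase treatment response for the 12 weeks of systemic therapy before resection, not for a contrast between arms. Response-type outcomes exist too: complete remission, and the radiological categories in the Discussion. This stands as far as it goes. The wording has a prognostic reading, and the stated model serves it. It does not remove the other reading, because in a randomised trial of surgery the impact of a marker on treatment response can naturally mean response to the randomised treatment.

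A reader might infer that the trial would thereby miss a declared patient-selection goal, since the Discussion closes with "we hope to provide stronger evidence for performance of PM and potentially better patient selection". The documents do not support that. The sentence ends a passage on ctDNA, whose aim is to identify patients at high risk of recurrence, and mutational status is not mentioned there. Any link is an inference, and the point does not need it.

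A further reply is that the article is condensed and the unseen analysis plan may add an interaction. It may. But the article does not leave this model open: it names an adjusted one.

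The last reply is low power, and the table above bears it out. Unknown mutation status would make it worse, and adjustment for about 15 sites may do so too. That argues for an estimate with a confidence interval and against a test.

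**Conclusion.** The point holds as a limited one. The stated model answers the prognostic reading of the mutational-status question and cannot answer the effect-modification reading. It would be too strong to say that the plan yields no estimate of the impact of mutational status: it yields the mutation HR. What it does not yield is any estimate of how the surgery effect varies by mutation.

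The conclusion about the model is structural and rests on no assumed figure. The precision figures rest on 83 deaths with known status and on an assumed p of 0.2 to 0.6: SE 0.44 to 0.55, CI factor about 2.4 to 2.9, ratio detectable with 80% power about 3.4 to 4.7. They concern OS only; the article gives no event number for PFS. The analysis is secondary or exploratory, so the issue is minor and does not touch the primary comparison or the sample size.

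**What to change.** Keep the main-effect model in Secondary Endpoints for Efficacy and say that it addresses the prognostic question. For OS and PFS, pre-specify an additional Cox model with a treatment-by-mutational-status term. Report the HR of surgery versus control within each mutation group and the ratio of HRs, each with a 95% CI, labelled exploratory and not used as a decision test. State beside the results how many patients and events had known mutation status.

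The cost is one further model term per endpoint on data the trial already plans to use. The downside is wide intervals: an inconclusive ratio must not be read as evidence that the effect is the same in both groups.
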